#### Exploratory Analyses

We plan to examine whether the amount of intervention (Quitline counseling, NRT) received by participants is related to outcomes. We will also explore different imputation strategies for missing data related to outcomes.

#### Economic Evaluation

A cost-effectiveness analysis of Quitlink will be conducted alongside the trial described here, using data 8 months post randomization. A modeled analysis will estimate future costs and benefits of smoking cessation beyond the trial period, over the life course. Full protocol details of this are presented in this Special Issue in Sweeney et al. (in submission). In brief, incremental cost-effectiveness ratios (ICER) will be calculated for the cost ($AUD) per successful quit and quality adjusted life year (QALY) gained (i.e., cost-utility) as a result of Quitlink when compared with usual care. Healthcare system and limited societal perspectives will be taken.

### Qualitative Evaluation

A nested qualitative study will be conducted. All interviews (participants and workers) will be audio recorded, transcribed, and a general inductive approach will be taken to the analysis (65).

#### Participant Interviews

Semi-structured individual in-depth interviews will be conducted with 72 participants. The (unblinded) qualitative researchers will access assessment data (REDCap) to view participants' cigarette consumption and service use data. They will use these data to purposively invite participants at each of the assessment timepoints (2-, 5-, and 8-months) for interview. Potential participants will be sent a flyer via text, mail, or email (depending on contact information available) asking them to participate in an interview. Upon affirmation, they will be provided the full Information Statement on the interview component.

#### Participant Selection

At 2 months, 30 participants will be interviewed (15 in each study arm, with cessation outcomes balanced across groups to negate any potential therapeutic effect of the additional qualitative interviews). The majority of the interviews (~10 per arm) will be with participants who have either not reduced smoking levels or have made only some reduction in smoking (<50%). Having a mix of those who have engaged with the intervention (attended 4+ Quitline sessions; or engaged in other treatments) and those who have not engaged or under-engaged (1–3 sessions) will enable identification of both barriers to engagement and barriers to change.

At 5 months, another 30 participants will be interviewed (15 per treatment arm, balanced for smoking outcomes). The majority (~10 per arm) will be “relapsers” (defined as those who have reduced consumption by 50–100% at 2 months but have resumed or increased use by 5 months), to allow a focus on medium term barriers to cessation maintenance, again with a mix of those who are engaged and those who are non- or under-engaged.

At 8 months, 12 participants will be interviewed (no balancing required as this is after primary endpoint collection), including ~6 who have relapsed (in order to focus on longer term barriers to cessation maintenance). At each time point, interviews will also be conducted with people who have successfully quit and maintained cessation to determine whether those who are successful face the same barriers as others but overcome them, and/or use the intervention in different ways. Participants in the qualitative study will be remunerated $40 for participation in individual interviews expected to take ~45 min.

#### Mental Health and Quitline Victoria Counselor Interviews

Interviews will evaluate the acceptability of the intervention among mental health practitioners (including peer workers) and Quitline counselors. Semi-structured individual in-depth interviews will be conducted with 15 mental health practitioners to enable data collection to reach saturation and for key themes to be identified (66). For Quitline counselors, three group interviews (4–5 counselors per group) will be conducted. Interviews with mental health practitioners and Quitline counselors will explore their experience of the program and its strengths and weaknesses from their perspective. Mental health practitioners will also be asked to focus on the implementation and sustainability of the Quitlink intervention.

### Data Safety Monitoring Board

A Data Safety Monitoring Board (DSMB) will be established. The DSMB will monitor safety and adverse events reported and will convene as required throughout the duration of the trial. The DSMB will be composed of individuals with appropriate expertise (e.g., clinical trials, statistical expertise, mental health expertise) who are independent from the study and free of conflict of interest, and where this is not practical, measures will be taken to minimize the perceived conflict of interest. The DSMB will have the capacity to contribute to decisions regarding continuation or discontinuation of the trial based on scientific and ethical factors. The DSMB will operate under the rules of an approved charter that will be written and reviewed by the DSMB. Each data element that the DSMB needs to assess will be clearly defined in the DSMB charter. The DSMB will provide its input to the Chief Investigator, and this will be reported to HRECs and other regulatory bodies as per local guidelines.

### Safety Monitoring

Adverse events (AEs) will be collected and reported as per Good Clinical Practice guidelines, from the point of enrolment until end of their participation. Follow-up assessors will prompt for all AEs as part of the interview schedule, while Quitline counselors will record any serious or severe events (SAEs) reported during counseling, as per current Quitline protocols, and will report these to research staff. If a participant withdraws from the study with an ongoing AE during the treatment phase, AEs will be followed up until it is resolved; or 7 days following withdrawal, at which time participants will be advised to contact their treating physician if AEs persist. The DSMB will review safety data on a regular basis, with SAEs and other significant safety issues reported immediately to the DSMB and further (e.g., governing ethics committee/s) as necessary as per local guidelines.

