### Standard Smoking Care

An active control condition, involving brief advice on the importance of quitting and provision of printed information on where to access assistance, is being utilized in this study as it reflects what is expected of mental health services as part of routine care (even though it is not routinely delivered).

The brief intervention provided to all participants includes advice to quit, encouragement to use NRT, and a Quit Victoria pack of written materials to motivate a quit attempt (e.g., costs of smoking and benefits of quitting) and resources to support self-management (e.g., Quitline phone number, “4Ds” strategy: ‘Delay, Deep-breathe, Drink water, Do something else’ to manage cravings; using NRT products).

With consent, a letter will be sent by the research team to nominated health professionals general practitioner (GP)/psychiatrist with information about their client's trial participation and a link to Australia's smoking cessation guidelines for health professionals, which includes a list of medications affected by smoking. No further intervention will be provided as part of the project for those in the control condition.

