##### Safety data

Adverse events will be collected at all follow-up time points, with prompting via questions asking how the participant has been feeling in general and if they have any health concerns.

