**INTERVENTION^*^**																		
Referral to Quitline		X																
Contacted by Quitline and smoking cessation initiated			X															
Quitline determines preferred oral NRT for second 4-week supply				X														
NRT dispensing		X		X														
Smoking cessation program			X	X	X	X	X	X	X	X								
FOLLOW-UP ASSESSMENTS											X			X			X	
Blinded follow up assessment conducted (all participants)											X			X			X	
Potential qualitative interviewees identified^**^											X			X			X	
Qualitative interviews conducted^**^												X			X			X
CO monitoring (on reported abstainers)																	X	

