**ADVERSE EVENTS**																		
Unprompted (serious/severe)			X	X	X	X	X	X	X	X								
Prompted (all)											X			X			X	

* *Intervention group only*.

** *Participants will be purposely selected at each of the assessment timepoints (2, 5, and 8 months) to be invited for interview*.

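### The only unprompted route described for serious events in weeks 1–8 runs through counseling scheduled in one arm, and severe events share the SAE label, so safety ascertainment may differ by arm

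*Protocol article*

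**What the plan says.** Safety Monitoring declares adverse event collection "from the point of enrolment until end of their participation", without distinguishing the arms. It then names two sources. Follow-up assessors prompt for all events, "while Quitline counselors will record any serious or severe events (SAEs) reported during counseling, as per current Quitline protocols", and the counselors pass these reports to research staff. SAEs are to reach the DSMB immediately.

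Table 2 (Stepwise Procedures) has two adverse event rows. The row labelled "Unprompted (serious/severe") is marked in weeks 1 to 8. The prompted row is marked in weeks 9, 21 and 34. Neither row carries the asterisk that restricts the intervention block to one arm.

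The Quitlink Intervention section schedules up to seven calls in 8 weeks, with structured monitoring of mental health symptoms, withdrawal and medication side-effects. For controls, Standard Smoking Care says: "No further intervention will be provided as part of the project for those in the control condition". The monthly texts described under Participant Recruitment and Retention go to participants generally, but their stated purpose is to keep contact details current.

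Safety data describes the prompted route: "Adverse events will be collected at all follow-up time points, with prompting via questions asking how the participant has been feeling in general". Table 2 applies it to both arms: "Blinded follow up assessment conducted (all participants"). Table 1 adds a question on hospitalizations and other intensive service use at 2 and 8 months.

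**The concern.** Arms that differ in contact during treatment will tend to differ in how many events are heard of, whatever the true risk. An intervention participant with an event in weeks 1–8 can tell a counselor at the time and an assessor at week 9. A control has only the second opportunity, and a control lost before week 9 may have none.

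The wording adds a second problem. Severity describes intensity; seriousness describes the consequence of an event. Putting both under the SAE label, in the sentence about counselors, means that a severe but non-serious event could go to the DSMB as an SAE, and this would happen mainly for Quitlink participants.

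The Data Safety Monitoring Board section lets the board contribute to decisions on continuing the trial. An imbalance produced by the reporting route could be read as harm.

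**Working it through.** The plan states no figure for this point, so the check is a trace of capture by arm, followed by an illustration.

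**Trace**

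| Period | Intervention | Control |
|---|---|---|
| Weeks 1–8 | Counselor records serious or severe events | No route described; Quitline contact only by self-referral |
| Week 9 | Prompted, blinded assessor; hospitalization item | The same |
| Week 21 | Prompted, blinded assessor | The same |
| Week 34 | Prompted, blinded assessor; hospitalization item | The same |

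The described capture differs only in weeks 1–8. From week 9 it is the same.

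**Illustration, with equal true risk in both arms**

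Inputs:
- *a*, attendance at 2 months: 0.70, borrowed from the roughly 30% attrition in Sample Size Determination. That figure inflates a sample size set for the 8-month outcome, so using it at 2 months is an assumption; 0.85 and 1.00 are also shown.
- *r*, chance that an attender reports the event: assumed, 0.6 to 1.0.
- *c*, chance that a counselor records it: assumed, 0.3 to 0.7.

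Control capture: s = a × r. Intervention capture, if the two routes are independent: 1 − (1 − s)(1 − c). The recorded-event ratio is the second divided by the first.

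| a | r | s | Intervention capture, c = 0.3 to 0.7 | Ratio |
|---|---|---|---|---|
| 0.70 | 0.8 | 0.56 | 0.692 to 0.868 | 1.24 to 1.55 |
| 0.70 | 1.0 | 0.70 | 0.79 to 0.91 | 1.13 to 1.30 |
| 0.85 | 0.8 | 0.68 | 0.776 to 0.904 | 1.14 to 1.33 |
| 0.70 | 0.6 | 0.42 | 0.594 to 0.826 | 1.41 to 1.97 |
| 1.00 | 1.0 | 1.00 | 1.00 | 1.00 |

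With recall of 0.8 to 1.0 the ratio is 1.13 to 1.55. Only the pessimistic recall of 0.6 takes it to 1.97.

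**Counts.** Assume 10% true risk and 191 per arm, which gives 191 × 0.10 = 19.1 true events per arm. With a = 0.70 and r = 0.8, controls record 19.1 × 0.56 = 10.7. The intervention arm records 19.1 × 0.692 = 13.2 to 19.1 × 0.868 = 16.6, and 19.1 × 0.78 = 14.9 at c = 0.5.

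**If the routes are not independent.** Suppose that those lost at 2 months are exactly those who never speak to a counselor. Counselors then add only events that attenders fail to report, and the ratio becomes [1 − (1 − r)(1 − c)] / r, with *c* now applying to attenders. At r = 0.8 this is 0.86/0.8 = 1.08 for c = 0.3 and 0.94/0.8 = 1.18 for c = 0.7.

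**The case against.** The strongest reply is that the article names one unprompted source without excluding others. The Table 2 row is not limited to the intervention arm, collection is declared for everyone from enrolment, and controls may self-refer to Quitline (Covariate or process measures). A condensed article may leave reporting pathways to the full protocol, and the DSMB charter is to define the board's data elements. This stands to the extent that one cannot say the route exists only in the intervention arm. It does not remove the mismatch: Table 2 implies capture for all in weeks 1–8, and the text names a source that is scheduled for one arm. Defining data elements would not equalise contact.

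Symmetric capture is also substantial. All adverse events are prompted in both arms at three time points, hospitalizations are asked about twice, and Statistical Methods keeps participants who miss an assessment in later follow-up. This stands. Control events can be recovered late, and the illustration gives no credit for the later contacts.

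A reader might infer three stronger things:
- **That the safety data are biased against Quitlink.** The documents support a risk and a probable direction. The capture rates are assumptions, and counseling is voluntary, so engagement and follow-up may go together and shrink the ratio.
- **That the between-arm comparison is uninterpretable because the sources are pooled.** No pooling rule and no between-arm test of SAEs is stated.
- **That the wording breaches Good Clinical Practice, or that every severe event will be counted as an SAE.** The article cites no specific rule. The sentence says what counselors record and pass on; it does not say how research staff then classify it.

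**Conclusion.** The point holds as a risk of differential ascertainment in weeks 1–8, together with a label that merges severe with serious events. The probable direction is more, and earlier, recorded SAEs under Quitlink. The size cannot be determined from the article. Under equal true risk, independent routes and the assumed rates, the recorded-event ratio is about 1.13 to 1.55. It is lower if disengagement from counseling and loss to follow-up coincide, and 1.00 with complete 2-month attendance and recall. Even at 1.00, reports would reach the DSMB earlier from one arm, and the merged label would still act mainly there. The primary outcome is unaffected. The change should be made because it is cheap and the DSMB relies on these reports.

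**What to change.** 1. Record the source of every adverse event. Base any between-arm safety comparison on the prompted events, which blinded assessors collect identically in both arms. Show counselor-reported events to the DSMB in full, but separately and labelled by source.
2. Replace the wording "any serious or severe events (SAEs") with classification as an SAE by seriousness alone, and record severity in its own field.
3. Reconcile the unprompted row of Table 2 with Safety Monitoring. State whether unprompted capture in weeks 1–8 applies to both arms and, if it does, by what route controls' events are received.

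The cost is one extra source field, a separate severity field, revised wording and a reporting rule. The downside is small: the by-arm comparison leaves out events known only through a counselor, though the DSMB still sees them.

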## Anticipated Results

This RCT will test the effectiveness of the Quitlink intervention for smoking cessation among SSMI. We anticipate that the intervention will be associated with significantly higher rates of continued abstinence from smoking at 8-month follow-up, relative to the control condition. We also anticipate the intervention will be more cost-effective compared to the control condition of usual care and reduced financial stress for participants. Using qualitative methods, we will also identify barriers and enablers to making and sustaining quit attempts. A range of secondary outcomes will be measured on follow-up occasions and we expect that the Quitlink intervention will be associated with significantly better outcomes on these variables (higher rates of 7-day point prevalence abstinence, quit attempts, smoking cessation motivation and self-efficacy, mental health, and quality of life and lower reported cigarette consumption, nicotine withdrawal symptoms, expenditure on cigarettes, and alcohol, and cannabis use).

## Ethics and Dissemination

Prior to participation in the trial, the person will be fully informed about the research and given ample time and opportunity to enquire about details and decide whether or not to participate. If they agree to participate they will be asked to sign the study specific consent form. To ensure anonymity and to limit disclosure, participants will be assigned a unique identifier at the time of randomization. Results arising from the RCT will be published in peer-reviewed journals and disseminated at international conferences. Results will be reported in such a way that participants will not be identifiable.

### Research Ethics Approval

Ethics approval has been obtained through St Vincent's Hospital, Melbourne (HREC Reference Number: HREC/18/SVHM/154), the University of Newcastle HREC (HREC Reference Number: H-2018-0192) and the Cancer Council Victoria, HREC (HREC Reference Number: 1807).

### Protocol Amendments

Each study site will only be able to start data collection once the relevant Ethics Committee approval is obtained. In the case of proposed protocol changes, an amendment will be submitted to the Ethics Committees for approval, and the trial coordinating center will ensure all study staff are provided with new documentation. Any significant protocol changes will be updated on the ANZCTR and reported in the final outcomes paper.

### Consent or Assent

The study is based on the principles of Good Clinical Practice according to the Declaration of Helsinki. Potential participants will be given oral and written explanation of the study including the potential risks, their right to withdraw at any time and the details of data protection and confidentiality and sufficient time to ask questions. A signed consent form will be obtained. Participants will be given the opportunity to agree or decline to being contacted for ancillary studies, without effecting participation in the main trial. A copy of the PICF will be given to the person.

### Confidentiality

The trial will be conducted in accordance with applicable Privacy Acts and Regulations. All information regarding trial participants will be treated in strict confidence. Participants' identifying details will be stored separately from other data. Participants will be informed of the potential reasons for breaching confidentiality in the PICF (risk of harm to self or others). Data, which identify any trial participant, will not be revealed to anyone not directly involved in the trial or the clinical care of that participant.

### Access to Data

All data will be considered the property of the trial chairperson, who, in consultation with the trial management committee, will be responsible for presentations and publications arising from this trial.

### Dissemination Policy

Trial findings will be summarized and posted to participants who have indicated they would like a copy of the results.

## Discussion

The Quitlink study is the first rigorously designed RCT to evaluate a specialized quitline intervention accompanied by NRT, for people with SMI, with biochemical verification of self-reported abstinence. Accessible smoking interventions like quitlines are clearly required to improve the mental and physical health of smokers in receipt of mental health treatment and links with mental health services are crucial to ensure maximum utilization. A major strength of this study is that it is demonstrably an intervention that can and will be used if the trial demonstrates it helps: it uses two strategies that are currently funded, i.e., quitline and peer workers, but not currently co-ordinated. Quitlines exist but are underutilized by those with SMI; likewise, peer workers are employed but do not uniformly see smoking cessation as part of their role. The study investigates a model for how these two existing strategies can be co-ordinated to maximize the health impact for SSMI, who often wish to quit but are not properly supported to do so. Having peer workers trained in assessment, brief smoking cessation advice, and proactive referral to quitline is more likely to attract SSMI to consider smoking cessation. It is a simple and potentially cost effective method of increasing access to smoking cessation services in the mental health sector.

### Limitations

There are three main limitations associated with this trial. Firstly, due to cluster randomization of residential sites, the peer workers will become aware of each site's allocation. Peer workers will be carefully trained and supervised not to communicate this information. They will also be supervised so as to encourage equal recruitment across control and intervention sites. Secondly, outcome to 8-months has been chosen as the focus of this study so as to examine medium term smoking, which parallels that for well populations (67). However, it would be informative to follow the sample over a longer timeframe to measure longer-term health and other benefits.

### Conclusions

If Quitlink is shown to be effective, it has the potential to greatly improve individuals' longevity, quality of life, mental health, and reduce health care costs. This is an innovative and practical service delivery model that has the potential to ensure that smokers with SMI have access to best-practice smoking cessation treatment. Secondly, regardless of effectiveness outcomes, the project's qualitative study will provide greater insights into the barriers faced by smokers with SMI and will assist in the development of even more effective interventions.

The intervention can be quickly and directly translated to quitlines and mental health services, to improve rates of smoking cessation among SSMI. Study findings will be of significant interest to consumer and carer groups, the broader community sector, as well as researchers and clinicians. The rigorous study design, inclusion of cost-effectiveness evaluation and qualitative study are key strengths.
